### Interventions

2.5

The study will select patients who meet the study criteria by recruiting them at the hospital. A randomized controlled study will be conducted, in which sodium hyaluronate will be used in the control group and the experimental group will include TC exercise on the basis of the control group. Patients in both groups will receive the same routine care, avoid alcohol, tobacco and irritating food, avoid strenuous exercise, and adverse reactions in patients during the test need to be concerned. If necessary, the attending doctor may adjust the treatment according to the patient's condition, and all interventions will be recorded in detail for final outcome analysis. Efficacy assessors are not aware of the study plan, and data statisticians are not involved in study design and implementation. The health of each patient will be assessed before and after the treatment, including observational indicators, and all patients will be followed up by telephone. The follow-up visit includes cardiovascular events and re-hospitalization.

(1)Control group: patients will be placed in the sitting or supine position, and the knee joint will be kept bent 70° to 90°, sterilized strictly, with sterile towel laid and aseptic operation performed. The lower lateral or inner side of the patella will be used as the conventional puncture point, and the knee joint cavity will be punctured through a 5 mL syringe. If there is joint effusion, it will be drained first, and then 20 mg sodium hyaluronate will be injected (Shandong Bausch Fruida Pharmaceutical Co., LTD., specification 2 mL:20 mg, CFDA approval number: H10960136); if not, 20 mg sodium hyaluronate can be directly injected into the joint cavity. After injection, help the patient to move the knee joint so that sodium hyaluronate can be evenly coated on the internal surface of the joint. One time/week, 5 times as a course of treatment. Health education should be carried out for patients to avoid acute jumping, walking up and down stairs, climbing mountains and other activities that damage joints, and remind them to pay attention to the warmth of joints as well. Pay attention to communicate with patients, be aware of their psychological and emotional changes, avoid or relieve anxiety, depression, and other adverse emotions of the elderly patients.(2)Experimental group: The experimental group will be given 24 simplified TC on the basis of conventional treatment. The subjects will be taught and practiced by professional TC teachers to ensure that the practice time and movement rhythm are basically consistent. The complete set of TC consists of 3 parts: preparation, training, and ending activities. It lasts for about 20 minutes per time, twice a day, once in the morning and once in the afternoon, and lasts for 5 weeks in total.

### Outcomes

2.6

#### Observation indicator

2.6.1

① Use Western Ontario and McMaster Universities Osteoarthritis Index^[18]^ and choose V3.1 Mandarin version. A total of 24 items will be evaluated in terms of pain, stiffness, and joint function. The value of each item will be recorded by visual analogue scale.^[19]^ The higher the score, the more serious the disease. ② Hospital for special surgery knee score^[20]^ will be used to evaluate the knee function of patients, and the total score of hospital for special surgery knee score is 0 to 100 points. The higher the score, the better the knee function of patients. ③ Balance index: Italian Tecnobody dynamic balance tester will be used to record the balance data of patients during dynamic trajectory measurement in B position (standing position, 50% load on 1 leg) before and after training. Items include anterior and posterior axis stability index, left and right axis stability index, A2 to A6 axis stability index, A4 to A8 axis stability index, and circular axis stability index before and 5 weeks after the treatment. ④ Hepatorenal function.

#### Efficacy indicator

2.6.2

Main efficacy indicators: total effective rate: according to *Guiding Principles for Clinical Research of New Chinese Medicine*,^[21]^ total effective rate = (clinical control + significantly effective number + effective number)/total number of people × 100%. ① Clinical control: pain and other symptoms disappear, joint activity is normal, integral reduction ≥95%; ② Significantly effective: pain and other symptoms disappear, joint activity is not limited, 70% ≤ integral reduction < 95%; ③ Effective: pain and other symptoms basically disappear, joint activity is slightly limited, 30% ≤  integral reduction < 70%; ④ Ineffective: no significant improvement in symptoms such as pain and joint activity, integral reduction < 30%.

Secondary efficacy indicators: changes in osteoarthritis index score, knee joint score, and balance index

#### Adverse event rate

2.6.3

Including the number of patients who experience any uncomfortable symptoms during treatment (such as dizziness, nausea, etc).

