**Methods::**

This is a prospective randomized controlled clinical trial. One hundred forty-six cases of KOA patients will be randomly divided into experimental group and control group according to 1:1 ratio, 73 cases in each group, the control group: sodium hyaluronate; experimental group: TC added on the basis of the control group. Both groups will receive standard treatment for 5 weeks and will be followed up for 3 months. Observation indicators include: the western Ontario and McMaster universities osteoarthritis index; hospital for special surgery knee score; balance stability index, liver and kidney function, adverse reaction rate, etc. SPSS 23.0 software will be used for data analysis.

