## Introduction

1

Knee osteoarthritis (KOA) is the most common degenerative joint disease involving cartilage and surrounding tissues, which is characterized by a series of variation such as changes in articular cartilage bone, osteophyte formation, and decreased joint muscle vitality.^[1]^ Clinical manifestations include joint pain, deformity, and reduced function,^[2]^ increasing the risk of fracture and fall.^[3]^ KOA is one of the common causes of mobility disorders and seriously affects the quality of life of patients.^[4,5]^ With the aggravation of population aging, KOA has become a public health problem that endangers global human health.^[6]^ According to statistics, more than 1/3 of the elderly suffer from KOA, and the disability rate is as high as 53%.^[7]^ As for the effective treatment of KOA, a large number of clinical and basic studies have been carried out at home and abroad, mainly including drug therapy, exercise therapy, and surgical treatment,^[8]^ all of which are aimed at relieving pain, delaying disease progression, protecting knee joint, and improving patients’ quality of life. As an important part of non-drug surgical treatment, exercise therapy has been recommended by several clinical guidelines as an effective method for the treatment of KOA.^[9–11]^

Tai Chi (TC), one of the traditional Chinese skills, is a defensive exercise with moderate intensity.^[12]^ It has become one of the most popular forms of exercise, which is rich in content and easy to learn, and is not restricted by space and time. It also emphasizes the integration of essence, qi and spirit combined with breathing to achieve the purpose of cultivating body and mind, preventing and treating diseases when exercising. Studies have found that TC exercise can increase muscle strength, improve balance and sensitivity.^[13]^ In recent years, studies on the effect of TC exercise on lower limb function of KOA patients have increased at home and abroad,^[14–16]^ but its clinical efficacy is still unclear.

Therefore, we intend to evaluate the effects of TC exercise on lower limb function and balance ability in patients with KOA in this randomized controlled trial.

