### Sample collection

2.7

Data will be collected according to the evaluation criteria before and 5 weeks after the treatment, and telephone follow-up will be conducted for 3 months after the treatment. If follow-up information cannot be collected, the reasons for loss of follow-up shall be recorded in detail. Access to the database is restricted to the researchers in this research group.

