### Study quality control

2.8

Throughout the trial, each participant will be monitored for safety. All adverse event occurrences will be referred to the office of the Clinical Research Ethics Committee, which will review the events and determine causal relationship. We will set Data and Safety Monitoring Board. Members of Data and Safety Monitoring Board include physicians, clinical pharmacists, trial method experts, statistical experts, and members of the ethics committee, who will conduct risk assessment and safety analysis procedures according to termination conditions.

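### The adverse event rate in 2.6.3 is worded by symptoms and by the treatment period, so symptom-free events and all follow-up events fall outside the between-arm comparison

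*Protocol article*

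**What the plan says.** Section 2.6.3 gives the only definition of the adverse event rate in the protocol article: "Including the number of patients who experience any uncomfortable symptoms during treatment (such as dizziness, nausea, etc". Section 2.9 then compares the incidence of adverse events between the two arms by chi-square test.

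Other sections reach wider:

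- Section 2.8: "Throughout the trial, each participant will be monitored for safety", and "All adverse event occurrences will be referred to the office of the Clinical Research Ethics Committee".
- Section 2.5, on the telephone contact: "The follow-up visit includes cardiovascular events and re-hospitalization". Section 2.7 gives its length: "telephone follow-up will be conducted for 3 months after the treatment".
- Section 2.6.1 lists "④ Hepatorenal function" as an observation indicator. The Abstract (Methods) places it beside the adverse reaction rate as a separate item: "balance stability index, liver and kidney function, adverse reaction rate, etc".
- The Introduction describes knee osteoarthritis as "increasing the risk of fracture and fall". Balance ability is part of the stated aim.

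**The concern.** The definition sets two conditions. The patient must experience something uncomfortable, and it must happen during treatment. Because it supplies the numerator of a tested comparison, anything that fails either condition is absent from that comparison, even where another section says the trial will look for it.

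Two consequences matter. First, events that the trial collects (cardiovascular events, re-hospitalization, abnormal liver or kidney results) have no stated place in the rate by which the arms are compared on safety. Second, falls are the event most likely to differ between arms, in either direction. Only the experimental arm does standing exercise, in patients up to 80 years old, and better balance is what the trial hopes to show. An uninjured fall is an event rather than a symptom, and no section shown asks about falls. The trial could report similar adverse event rates without having counted them.

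**Working it through.** The documents state no figure to reproduce on this point, so the check sets the sections side by side. Each type of event is tested against the two conditions in 2.6.3.

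| Event | Felt as a symptom? | During treatment? | Counted under 2.6.3? | Collected elsewhere? |
|---|---|---|---|---|
| Painful fall or fracture in the 5 treatment weeks | Yes | Yes | Yes | No separate item shown |
| Fall without injury or discomfort in the 5 treatment weeks | No | Yes | No | No item shown |
| Silent liver or kidney abnormality at the 5-week test | No | First seen at or after the end of treatment | No | Yes, 2.6.1 |
| Cardiovascular event or re-hospitalization in follow-up | Usually | No | No | Yes, 2.5 |
| Any other event in follow-up | Either | No | No | No item shown |

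Three observations follow.

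1. **Symptom condition.** The open-ended words in 2.6.3 widen the list of symptoms, but each counted item must still be an uncomfortable symptom. A laboratory value or a harmless fall is not one.

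2. **Time condition.** Treatment lasts 5 weeks and follow-up 3 months. Taking 3 months as about 13 weeks, observation runs 5 + 13 = 18 weeks. The definition covers 5/18 = 28% of that time, and 13/18 = 72% lies outside it. Section 2.8 sets no such limit on safety monitoring.

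3. **Hepatorenal results.** Section 2.7 places data collection before treatment and at the 5-week point. Whether that point means the end of the 5-week course or 5 weeks after it, a symptom-free abnormality found there fails the symptom condition. Nothing shown says whether such a result counts as an adverse event. The Discussion groups intra-articular sodium hyaluronate, which both arms receive, with drugs for which it lists liver and kidney damage among the adverse reactions.

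The difference in exposure between arms comes from 2.5. The experimental arm does about 20 minutes of Tai Chi twice a day for 5 weeks. If every day is used, that is 2 × 7 × 5 = 70 sessions and 70 × 20 = 1,400 minutes, or about 23 hours. The control arm does none.

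**The case against.** The strongest reply is that 2.6.3 is one loosely worded line in a condensed article and should not be read as a closed list. It opens with a word of inclusion, covers any uncomfortable symptom, and ends its examples with an etcetera. This stands in part: a fall or fracture during treatment that hurts can be counted. It does not remove the symptom condition or the time condition.

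Three stronger readings are tempting, and the documents do not support them.

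- A reader might infer that falls, fractures and laboratory harm never reach the safety results, or that 2.6.3 is the only safety outcome. They are not wholly lost. Hepatorenal function is an indicator in its own right, and cardiovascular events and re-hospitalization are collected at follow-up.
- A reader might infer that a silent abnormality escapes the referral in 2.8. That section covers all adverse event occurrences and is not tied to the wording of 2.6.3. It also sets up a Data and Safety Monitoring Board. An escape from referral is a guess.
- A reader might attach a number of missed falls. The documents give no fall rate, so any figure would be invented.

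Two further points are fair. The Introduction names falls and fractures as consequences of the disease, not as a hazard of Tai Chi, and the Discussion says no serious adverse events related to Tai Chi have been reported. The lack of a fall count is therefore a missed opportunity rather than a contradiction. Laboratory thresholds and telephone scripts may also sit in the full protocol, and their absence here is no fault. What remains is a definition that is stated and does not fit its neighbouring sections.

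**Conclusion.** The point holds in a limited form. As worded, the incidence compared in 2.9 omits symptom-free events and everything in the 3-month follow-up. This does not fit the trial-long monitoring in 2.8, the follow-up events in 2.5 or the hepatorenal measurements in 2.6.1.

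The size can be given only in time: about 72% of the observation period lies outside the definition, taking 3 months as 13 weeks. The number of events affected cannot be derived from the documents. The conclusion assumes that the line in 2.6.3 is the operative definition for the comparison in 2.9. No other definition is shown. The primary efficacy comparison is not affected. This is an inexpensive improvement to the safety comparison, best made before enrolment because uninjured falls are hard to recover afterwards.

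**What to change.** Reword 2.6.3 so that an adverse event is any untoward medical occurrence, symptomatic or not, from first treatment to the end of follow-up, in line with 2.8. State that new out-of-range liver or kidney results at the 5-week test count toward it, and that the follow-up events in 2.5 do too. Record falls, with or without injury, as a separate line by arm. Put the same question to both arms at the existing visit and telephone contacts, so that closer contact with Tai Chi teachers does not by itself produce more recorded falls in the experimental arm.

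The cost is a few lines of text and one or two added questions, with no new visits or tests. The reported adverse event rate will be somewhat higher in both arms. Showing the treatment period and the follow-up separately would keep the during-treatment count readable.

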### Sample collection

2.7

Data will be collected according to the evaluation criteria before and 5 weeks after the treatment, and telephone follow-up will be conducted for 3 months after the treatment. If follow-up information cannot be collected, the reasons for loss of follow-up shall be recorded in detail. Access to the database is restricted to the researchers in this research group.

### Study quality control

2.8

Throughout the trial, each participant will be monitored for safety. All adverse event occurrences will be referred to the office of the Clinical Research Ethics Committee, which will review the events and determine causal relationship. We will set Data and Safety Monitoring Board. Members of Data and Safety Monitoring Board include physicians, clinical pharmacists, trial method experts, statistical experts, and members of the ethics committee, who will conduct risk assessment and safety analysis procedures according to termination conditions.

### Statistical analysis plan

2.9

Use Excel to build database. Full analysis set: including all subjects randomly enrolled, treated and visited at least once, and use full analysis set for intent-to-treat analysis. Per-protocol set: including all subjects who comply with the trial protocol, have no missing baseline variables, and have measurable major variables. Safety set: including subjects randomly enrolled, treated at least once and being safe after at least 1 treatment.

SPSS25.0 statistical analysis software will be used for data analysis in this study. If measurement data meet normal distribution, independent-sample *t* test will be used between groups and paired-sample *t* test will be used within groups; if not, non-parametric test will be used and the results will be expressed in quartiles; Chi-square test will be used for counting data. The incidence of adverse events is compared by chi-square test. When *P* *<* *.05*, the difference is statistically significant.

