### Patients

2.3

Diagnostic criteria: revised according to the diagnostic criteria for KOA from the American College of Rheumatology^[17]^: ① Patients with knee pain for most of the month; ② Radiographs shows osteophyte formation along the joint margin; ③ Joint fluid examination is consistent with osteoarthritis; ④ Age: ≥40 years old; ⑤ Morning stiffness ≤30 minutes; ⑥ Patients who have bone frictions in joint movement. Those who meet the criteria of ① + ②, ① + ③ + ⑤ + ⑥, or ① + ④ + ⑤ + ⑥ can be diagnosed as KOA.

Inclusion criteria: ① Patients who meet the diagnostic criteria of KOA; ② Age: ≥40 and ≤80 years old; ③ Patients who have certain communication and understanding ability, and can express their own will correctly; ④ Patients who voluntarily accept corresponding treatment and can cooperate; ⑤ Patients who sign the informed consent.

Exclusion criteria: ① Patients who suffer from acute systemic illness; ② Patients who have severe impairment of limb function; ③ Patients who have relative or absolute contraindications of rehabilitation exercise such as blood pressure descent during exercise; ④ Patients combined with hematopoietic system abnormalities; ⑤ Patients combined with severe mental illness; ⑥ Patients who are allergic to sodium hyaluronate; ⑦ Patients who are unable to understand the study protocol or unwilling after explanation.

Elimination criteria: ① Patients with serious adverse events or serious complications, which is not suitable for the next step; ② Patients with poor compliance, affecting the judgment of effectiveness and safety; ③ Patients whose disease progresses during the treatment and need to change treatment plan; ④ Patients who ask to withdraw from the study for any reason.

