### Sample size

2.4

Since the main efficacy index of this study is the total effective rate, the sample size will be estimated according to the total effective rate of pre-experiment. According to the preliminary clinical pre-experiment, the total effective rate of TC combined with sodium hyaluronate was 91.3%, and that of sodium hyaluronate was 68.57%. PASS15.0 will be used for sample size estimation, and an optimal design will be adopted. α = 0.05, β = 0.2, test efficiency = 0.8, the number of experimental group: the number of control group = 1:1, threshold = –0.4. According to the software calculation, the total sample size of the 2 groups will be 130 cases, and 146 cases will be finally included considering the clinical shedding rate of about 10%. The included patients will be numbered according to the order of treatment and divided into the treatment group and the control group by completely random method, with 73 cases in each group.

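### The safety set makes a safe outcome a condition of entry, so the adverse-event rate taken from it would be zero or understated

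*Protocol article*

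**What the plan says.** Section 2.9 (Statistical analysis plan) sets three conditions: "Safety set: including subjects randomly enrolled, treated at least once and being safe after at least 1 treatment". It later adds "The incidence of adverse events is compared by chi-square test", without naming the analysis set for that test.

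Section 2.6.3 (Adverse event rate) describes the endpoint as "Including the number of patients who experience any uncomfortable symptoms during treatment". Section 2.8 (Study quality control) states "Throughout the trial, each participant will be monitored for safety" and refers every adverse event to the ethics committee's office.

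The elimination criteria in section 2.3 (Patients) include "Patients with serious adverse events or serious complications, which is not suitable for the next step". They do not say whether such patients remain in any analysis set.

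**The concern.** A safety population is normally fixed by exposure: who was treated, and sometimes whether a safety assessment exists. Here the third condition is the result of that assessment. The only patients it can remove are those who were harmed, so any adverse-event rate computed in the set is too low or unaffected, never too high.

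The trial adds Tai Chi twice a day to weekly injections in patients up to 80 years old, and adverse events are a declared outcome. A rule that can take events out of numerator and denominator together would give false reassurance about the added exercise.

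**Working it through.** The article gives no adverse-event rate, and no stated calculation rests on this definition, so there is no figure to reproduce. The check compares the wording with the rest of the article and then works through two literal readings with assumed rates.

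**Inputs.** Arm size: "with 73 cases in each group" (section 2.4). Injections: "One time/week, 5 times as a course of treatment" (section 2.5). Adverse-event rates are assumed: 5–10% in the control arm and 5–30% in the experimental arm.

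**Step 1: the wording side by side.** Section 2.6.3 counts anyone with any uncomfortable symptom. Section 2.8 monitors every participant. Section 2.9 admits only those who were safe after at least one treatment. The first two describe a rate over all treated patients, which a set restricted by safety outcome cannot be relied on to give.

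**Step 2: strict reading (any adverse event disqualifies).** With *a* events among 73 patients, the set keeps 73 − *a* patients and 0 events. P-values are chi-square without continuity correction.

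| Assumed rates, control vs experimental | All treated patients | p | Strict safety set |
|---|---|---|---|
| 5% vs 5% | 4/73 vs 4/73 | 1.0 | 0/69 vs 0/69 |
| 10% vs 10% | 7/73 vs 7/73 | 1.0 | 0/66 vs 0/66 |
| 5% vs 15% | 4/73 vs 11/73 | 0.056 | 0/69 vs 0/62 |
| 10% vs 20% | 7/73 vs 15/73 | 0.064 | 0/66 vs 0/58 |
| 10% vs 30% | 7/73 vs 22/73 | 0.0019 | 0/66 vs 0/51 |

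For the last row, χ² = 146 × (22×66 − 7×51)² / (73 × 73 × 29 × 117) = 9.68. Under the strict set the event total is zero in every row, so expected event counts are zero and the statistic is undefined.

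**Step 3: loose reading (safe after at least one treatment is enough).** A patient is excluded only if unsafe after every treatment received. With an independent risk *q* per injection and five injections, the proportion with any event is 1 − (1 − *q*)⁵ and the proportion excluded is *q*⁵:

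- *q* = 2%: 9.6% have an event; 0.0000003% are excluded.
- *q* = 5%: 22.6% have an event; 0.00003% are excluded.
- *q* = 10%: 41.0% have an event; 0.001% are excluded.

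Independence makes the bias negligible. It fails for events that persist, and for patients who stop after a reaction to their first treatment, because that treatment is then the only one they received. If *s* such patients are removed from an arm with *a* events, the rate becomes (*a* − *s*)/(73 − *s*). This is below *a*/73, because 73(*a* − *s*) − *a*(73 − *s*) = −*s*(73 − *a*), which is negative. The range runs from no effect (*s* = 0) to the strict result (*s* = *a*).

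**Step 4: the between-arm difference on the loose reading.** Start from 22/73 vs 7/73, a difference of 30.14% − 9.59% = 20.55 points, and assume *s* = 3 in one arm only.

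- Removed from the experimental arm: 19/70 − 7/73 = 27.14% − 9.59% = 17.55 points.
- Removed from the control arm: 22/73 − 4/70 = 30.14% − 5.71% ≈ 24.4 points.

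Incidence falls in whichever arm loses patients, but the difference can shrink or grow.

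**The case against.** The best defence is that the condition requires safety after at least one treatment, not freedom from events throughout. A patient who is dizzy after the first injection and well after the second meets it, and the event is counted. This stands. A reader might infer that anyone harmed at the first treatment is out, or that the rate must go to zero. The words do not support that in general; the zero-event tables hold only on the strict reading.

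Second, sections 2.6.3 and 2.8 suggest that the authors meant having safety data after at least one treatment, and that the English slipped. That is likely. Requiring a post-treatment assessment would be a common and defensible convention, and no complaint is made against it. But the article nowhere states that meaning, and an analyst who follows the text has no other definition to use.

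Third, section 2.9 does not tie the chi-square test to the safety set. This also stands. The link is inferred from the set's evident purpose, and if the test were run on another set, this definition would not affect it.

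Fourth, a reader might infer from section 2.3 that patients with serious adverse events are removed from the safety analysis. The article does not say so. The criterion concerns patients unsuited to continue and is silent on analysis sets. That silence is worth closing, but it is not evidence of removal.

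**Conclusion.** The definition is wrong as written: entry to the safety set depends on the safety result, and nothing in the article corrects it. On the strict reading the comparison is empty at any event rate. On the loose reading incidence is understated, from negligibly if events are independent across injections to materially if harm persists or leads to stopping after the first treatment. The direction of bias in the between-arm difference is then not fixed.

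This rests on two assumptions: that the adverse-event comparison uses the safety set, and that the published wording will be applied. All event counts above are illustrative. The defect is one of wording, probably unintended, and not evidence that the trial means to discard events.

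**What to change.** In section 2.9, replace the definition with: *Safety set: all randomised patients who received at least one study treatment, whatever adverse events occurred.* Add that the adverse-event comparison uses this set, and that patients eliminated under section 2.3 for serious adverse events stay in the set and in the adverse-event count.

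If the sponsor does intend to require a post-treatment safety assessment, the text should say that the assessment must exist, whatever its result.

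The cost is two or three sentences. No treatment, visit, data collection or sample size changes.

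### Secondary function and balance scores: the planned unadjusted t test is valid but less precise than ANCOVA using the baseline already collected

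*Protocol article*

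**What the plan says.** Section 2.9 (Statistical analysis plan) makes the choice of test depend on the data. The condition is "If measurement data meet normal distribution"; where it is met, "independent-sample *t* test will be used between groups and paired-sample *t* test will be used within groups"; and "if not, non-parametric test will be used and the results will be expressed in quartiles". No baseline-adjusted model is named.

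Section 2.6.2 defines the outcomes concerned: "Secondary efficacy indicators: changes in osteoarthritis index score, knee joint score, and balance index". A baseline exists for each. Section 2.7 states "Data will be collected according to the evaluation criteria before and 5 weeks after the treatment", and section 2.6.1 repeats the timing for the balance measurements ("circular axis stability index before and 5 weeks after the treatment").

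The primary outcome is different in kind. Section 2.4 says that "the main efficacy index of this study is the total effective rate", a binary outcome, and section 2.9 assigns count data to a chi-square test.

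**The concern.** The aim given in the abstract and introduction is lower limb function and balance. Balance does not enter the definition of the total effective rate, and function enters it only through joint activity and a percentage reduction in an integral score. The secondary continuous scores therefore carry much of the answer to the trial's own question, and the whole of the answer on balance.

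Three features of section 2.9 weaken that answer.

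- **No baseline adjustment.** A change-score test subtracts the whole baseline and so over-corrects for chance imbalance; a test on the post-treatment score alone does not correct for it. Section 2.4 describes simple randomisation without stratification, so nothing in the described design limits such imbalance.
- **Test chosen from the data.** Moving from a comparison of means to a non-parametric test according to observed normality leaves the estimated quantity unfixed, and it may differ from one score to the next.
- **Within-group paired tests.** Both arms receive sodium hyaluronate (section 2.5), so improvement is expected in both. A paired test in either arm does not estimate the effect of Tai Chi.

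**Working it through.** **Plan's own figure.** There is none to reproduce for these scores: no SD, expected difference or power is given for them. The section 2.4 calculation ("α = 0.05, β = 0.2, test efficiency = 0.8", 130 evaluable patients) is for the binary primary. Only the number per arm is taken from it: 130/2 = 65.

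**Assumptions.** Two-sided α of 0.05 (the article does not state sidedness), equal SDs at baseline and 5 weeks, and a correlation r between them. The documents do not give r; 0.3, 0.5 and 0.7 are used. Effects are in SD units.

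**Variance of the treatment difference, relative to a t test on the post-treatment score alone:**

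- post-treatment score only: 1
- change score: 2(1 − r)
- ANCOVA: 1 − r²

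Hence ANCOVA / change = (1 − r²) / [2(1 − r)] = (1 + r)/2, and ANCOVA / post-only = 1 − r².

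| r | Change, 2(1−r) | ANCOVA, 1−r² | ANCOVA / change | ANCOVA / post-only |
|---|---|---|---|---|
| 0.3 | 1.40 | 0.91 | 0.65 | 0.91 |
| 0.5 | 1.00 | 0.75 | 0.75 | 0.75 |
| 0.7 | 0.60 | 0.51 | 0.85 | 0.51 |

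**Where the difference comes from.** Given a chance baseline difference D, the expected change-score difference is the true effect minus (1 − r)D, and the expected post-only difference is the true effect plus rD. ANCOVA removes both terms. The pieces add up: (1 − r²) + (1 − r)² = 2(1 − r), and (1 − r²) + r² = 1. The extra variance of each simpler test is exactly the chance imbalance left in it.

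**Equivalent sample size, change-score test against ANCOVA.** 1/0.65 = 1.54, 1/0.75 = 1.33 and 1/0.85 = 1.18, so ANCOVA is worth 54%, 33% and 18% more patients.

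**Detectable difference at 65 per arm and 80% power.** (1.960 + 0.842) × √(2v/65), where v is the relative variance. For v = 1 this is 2.802 × 0.1754 = 0.491 SD.

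| r | Post-only | Change | ANCOVA |
|---|---|---|---|
| 0.3 | 0.491 | 0.581 | 0.469 |
| 0.5 | 0.491 | 0.491 | 0.426 |
| 0.7 | 0.491 | 0.381 | 0.351 |

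For a true effect of 0.491 SD, power at r = 0.3, 0.5 and 0.7 is 65.8%, 80.0% and 95.1% with change scores, and 83.6%, 89.9% and 97.5% with ANCOVA.

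**Direction.** (1 + r)/2 is below 1 for every r < 1, and 1 − r² is below 1 for every r other than 0. ANCOVA is therefore more precise than both alternatives for any r strictly between 0 and 1. Only the size of the gain depends on the assumed value.

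**The case against.** The strongest reply is that nothing here is an error. Randomisation makes the between-group t test unbiased, whether run on change or on the final score. The outcomes are secondary, and no stated power target for them fails. This stands, and it limits the point to precision and interpretability.

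Some stronger readings are tempting, but the documents do not support them.

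- *The analysis ignores baseline.* A reader of section 2.9 alone might infer this. Section 2.6.2 speaks of changes in the scores, so a change-score test, which does use baseline, is the more natural reading. The post-only ratios, including the 51% at r = 0.7, apply only if that reading is wrong.
- *The plan uses the least efficient analysis available.* Change scores do better than post-only scores when r exceeds 0.5 and worse when it is below, so no such ranking holds over the assumed range.
- *Efficacy will be claimed from the paired tests.* The between-group test is named first, and nothing says that conclusions will rest on within-group results. The article is simply silent on how they will be used.
- *Quartiles will replace a treatment difference.* The text describes how non-normal data are summarised. It does not exclude an effect estimate, and a condensed article may leave that detail to the full plan.

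It is also true that the gain may be small. At r = 0.7 the detectable difference falls only from 0.381 to 0.351 SD against change scores. Against a post-only test at r = 0.3 the saving in variance is 9%.

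The reply does not establish that this is a detail left to an unseen plan. Section 2.9 names the tests, so the choice has been made and can be improved.

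**Conclusion.** The point holds as a recommendation about precision for the secondary continuous outcomes. It does not show bias, and it does not touch the chi-square comparison of the total effective rate. On the change-score reading, ANCOVA cuts the variance by 35%, 25% or 15% at r = 0.3, 0.5 or 0.7. On the post-only reading the cut is 9%, 25% or 49%. These sizes rest on equal SDs and an assumed r; the direction does not depend on which r between 0 and 1 is true.

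Two lesser matters belong with it: the choice between a mean comparison and a non-parametric test should not depend on the observed data, and within-group tests cannot support a conclusion about Tai Chi. The change should be made, but the trial does not depend on it.

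**What to change.** In section 2.9, for WOMAC, HSS and each balance index:

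1. Analyse the 5-week score by ANCOVA, with arm as factor and the same score at baseline as covariate. Report the adjusted mean difference with its 95% confidence interval.
2. Remove the normality-dependent switch of test. If residuals are skewed, keep the model and use robust or bootstrap standard errors. Quartiles may remain as descriptive summaries.
3. Present within-arm changes descriptively, and state that no conclusion about Tai Chi will be drawn from within-group paired tests.

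The primary analysis needs no change on this account. The cost is a few sentences in section 2.9. The baseline scores are already collected, ANCOVA is available in SPSS, which is already planned, and neither sample size nor visits change. The revision should be made before outcome data are examined.
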